### Sample size

The trial is designed to detect a reduction in hospitalisation or mortality rate of 7.5% at 1 year in patients identified with cardiac dysfunction from 15% anticipated in patients randomised to the standard pathway.^9^ Given approximately one third of patients in both randomised arms are estimated to have cardiac dysfunction, a 7.5% reduction would be diluted to a 9% overall reduction in the enhanced pathway arm. To detect a reduction in events from 15% to 9% (equivalent to a HR equal to 0.58) using log-rank analysis with an overall type 1 error rate of 0.05 (two-sided analysis) and a power of 0.90 requires a total of 146 events to be observed in at least 1070 participants (nQuery Advisor assuming 18-month recruitment) inflated to 1200 in anticipation of minimal drop-out.

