### Data collection

A clinical research co-ordinator (CRC) will collect information on demographic characteristics such as gender, age, vital signs, height and weight and medication history. The patients’ medical history will be taken along with pacemaker data (implant date, implanted device, programmed pacemaker mode, BR and cumulative pacing percentages), and blood draw will be obtained. Biological specimens will be analysed and stored in the onsite research pathology laboratory. Patients randomised to intervention will undergo a baseline transthoracic echocardiogram, which will be assessed by the CRC. All data will be stored anonymously and will be locked once complete.

To ensure protocol adherence, a single research team will undertake all study-specific activity and be regularly monitored.

Digital follow-up will occur at 12-month postrecruitment to record mortality and hospitalisation data and changes to medical therapy. Patient data regarding cardiac transplatation or device upgrade will be recorded and subsequently reported.

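### The dilution step in the sample size is wrong: a 7.5-point reduction in one third of patients gives 12.5% overall, not 9%, so power at 146 events is about 22%, not 90%

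*Protocol article*

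**What the plan says.** All the figures are in the Sample size section of the protocol article. The target effect is "a reduction in hospitalisation or mortality rate of 7.5% at 1 year in patients identified with cardiac dysfunction", starting "from 15% anticipated in patients randomised to the standard pathway". The share affected follows: "Given approximately one third of patients in both randomised arms are estimated to have cardiac dysfunction". The section concludes that "a 7.5% reduction would be diluted to a 9% overall reduction in the enhanced pathway arm". The next sentence uses 9% as the event rate in the intervention arm: "To detect a reduction in events from 15% to 9% (equivalent to a HR equal to 0.58". With "an overall type 1 error rate of 0.05 (two-sided analysis) and a power of 0.90", the log-rank comparison "requires a total of 146 events to be observed in at least 1070 participants", inflated to 1200 for drop-out.

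Under Statistical analysis plan, the primary analysis covers all randomised patients. The diluted effect is therefore the one the trial tests.

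**The concern.** A diluted effect cannot be larger than the undiluted one, so a 7.5% reduction cannot become a 9% reduction. If 9% is instead the resulting event rate, as the next sentence treats it, the overall drop is 6 points. That is most of the 7.5 points, although only one third of patients are said to benefit.

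The stake is how the result is interpreted. If identifying and treating dysfunction halves events in the affected third, as the plan assumes, the all-patient comparison would usually be non-significant. Readers told that the trial had 90% power would take this as evidence that screening does not work.

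**Working it through.** **Inputs** (Sample size section unless stated): control risk at 1 year 15%; reduction in patients with dysfunction 7.5 points; share with dysfunction 1/3; two-sided alpha 0.05; power 0.90; 146 events; 18-month recruitment. Allocation is 1:1 (Randomisation and interventions). Follow-up is at least 12 months (Methods and analysis).

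**1. The plan's own figure, taking 9% as given.**
- HR = ln(1 − 0.09)/ln(1 − 0.15) = 0.580.
- Events (Schoenfeld) = 4 × (1.96 + 1.2816)² / (ln 0.580)² = 142. The Freedman formula gives 149.
- The stated 146 lies between these, and power at 146 events is 91%. The event calculation is sound for 15% against 9%.

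**2. The dilution step.**
- Intervention-arm rate = (2/3 × 15%) + (1/3 × 7.5%) = 12.5%, a drop of 2.5 points.
- HR = ln(0.875)/ln(0.85) = 0.822.
- A 6-point overall drop would need 6 × 3 = 18 points in the affected third, or 6/7.5 = 80% of patients with dysfunction. With 15% as the risk in that third, removing every event there still leaves 10% overall.

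**3. Power at HR 0.822.** Power = Φ(√d/2 × |ln 0.822| − 1.96), where |ln 0.822| = 0.196.

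| Events, d | Basis | Power |
|---|---|---|
| 146 | stated target | Φ(1.19 − 1.96) = 22% |
| 165 | 1200 × (15% + 12.5%)/2, at 12 months | 24% |
| about 272 | 1200 patients, uniform 18-month accrual, 12-month minimum follow-up to a common end date, constant hazards, no drop-out | 37% |

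Events for 90% power = 4 × (1.96 + 1.2816)² / (ln 0.822)² = 1,089. That is 1,089/0.1375 = about 7,900 patients at 12 months, or about 4,800 with the accrual and follow-up in the last row.

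**4. Other readings of the inputs.**
- Prevalence 40%, as in the pilot cohort (Risk model): 15% − 0.4 × 7.5% = 12.0%, HR 0.79, power 31% at 146 events.
- Two thirds affected, as if the weights had been swapped: 10%, still not 9%.
- 15% as the risk only in patients with dysfunction: the overall difference stays at 2.5 points. The risk in the others is not given, so I take 0% to 15% as an assumed range:

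| Risk in the others | Control rate | Intervention rate | HR | Events at 12 months, 1200 patients | Power |
|---|---|---|---|---|---|
| 0% | 5.0% | 2.5% | 0.49 | 45 | 66% |
| 5% | 8.3% | 5.8% | 0.69 | 85 | 40% |
| 10% | 11.7% | 9.2% | 0.78 | 125 | 30% |
| 15% | 15.0% | 12.5% | 0.82 | 165 | 24% |

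**The case against.** The strongest objection is that 9% is unreachable only if patients with dysfunction also have a 15% risk. If 15% is the all-patient rate, the risk in the affected third could be higher, and a risk of 36% halved in one third gives exactly 15% to 9%. Benefit could also extend beyond that third, because the intervention package includes the pacing-avoidance algorithm and the pilot behind it excluded known LVEF below 50%. Both points are fair as possible routes to 9%. Neither is in the plan: the Sample size section takes 15% as the starting rate and derives 9% from diluting 7.5 points. Whatever the baseline risk, 7.5 points in one third is 2.5 points overall.

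Second, 22% is power at a fixed 146 events, and follow-up to a common end date would yield more. This stands, and is why 37% is shown. The Data collection section, however, describes outcome follow-up at 12 months, which supports the 24% figure. Even the extreme case of no risk at all in patients without dysfunction, with the longer follow-up, reaches only about 87%.

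Third, an added analysis by predicted risk is something a separate analysis plan may hold, and it would have limited power. I agree, and treat it as optional.

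**Conclusion.** The concern holds. From the plan's stated inputs the diluted intervention-arm rate is 12.5% (HR 0.82), not 9% (HR 0.58). Power is about 22% at the stated 146 events, 24% at 12 months in 1200 patients, and at most about 37% with longer follow-up under constant hazards and no drop-out. These figures assume 15% control risk, one third affected, a 7.5-point reduction in that third and no effect elsewhere, as the dilution sentence implies. None of the alternative readings examined for 1200 patients restores 90%. The calculation of 146 events from 15% against 9% is correct; the error is in the derivation of the 9%. It must be corrected because every later figure in the section depends on it.

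**What to change.** In the Sample size section:

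1. Replace the diluted figure with an intervention-arm rate of 12.5% (HR 0.82), and drop the description of 9% as a reduction.
2. Restate the power for that effect: about 22% at 146 events, with the 12-month and longer follow-up figures if wanted.
3. Say that 146 events give 90% power only for an overall HR of about 0.58, and that this needs more benefit than 7.5 points in one third of patients. If the sponsor had a higher risk in dysfunction or benefit outside it in mind, state that assumption and its basis.
4. State that a non-significant primary result will not be read as absence of benefit in patients with dysfunction.

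Optionally, pre-specify one supportive analysis of treatment effect by predicted risk of dysfunction at baseline. A subgroup by measured LVEF is not available in both arms, since "Patients randomised to intervention will undergo a baseline transthoracic echocardiogram" and no such scan is described for controls. The model variables come from the baseline history, pacing data and blood draw. NT-proBNP could be added, on the assumption (from the BNP-related aims) that it is measured in both arms. Its power will be low, so it should be labelled supportive.

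The cost is a reworded section, a less favourable stated power and at most one extra analysis. No additional patients are needed.

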### Pilot data

#### Risk model

The design of the OPT-PACE trial is informed by an observational cohort^11^ including 491 patients listed for a pacemaker generator replacement in a single tertiary centre (Leeds Teaching Hospitals NHS Trust) invited for pacing therapy information, diagnostic pacing data and an echocardiogram.

Of this cohort, 40% had a left ventricular ejection fraction (LVEF) of <50%, which was much higher (59%) in those with >80% RV pacing (p<0.001), demonstrating that patients with RV pacemakers have a high prevalence of LVSD. After a mean follow-up time of 668 days, 56 patients (12%) had died or been hospitalised for HF.

Multivariable analyses identified a number of simple clinical variables; high percentage RV pacing, high serum creatinine and previous myocardial infarction as potential independent predictors of LVSD to identify patients who may benefit from a more comprehensive review.^11^ This risk model requires external validation planned within the OPT-PACE trial.

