### Intervention development

The design of the pacemaker optimisation intervention used in the OPT-PACE trial is based on data from an observational cohort of 66 patients, referred for pacemaker generator replacement, recruited consecutively from a single tertiary centre (Leeds Teaching Hospitals NHS Trust).^9^ All patients recruited had been referred for pacemaker generator replacement. Exclusion criteria were inability to consent, underlying complete heart block, a life expectancy of <1 year in the opinion of the clinician (eg, terminal malignancy), the presence of a device-related complication or those with known LVEF <50%.

In patients recruited with avoidable RV pacing, a prespecified protocol was followed to reduce this as outlined in figure 1, including a reduction in the diurnal base rate (BR) to 50 beats/min with nocturnal rate or hysteresis to 40 beats/min along with the deactivation of rate-adaptive pacing. In addition, where sinus rhythm and heart block had been documented, the atrioventricular delays were extended or a device with RV avoidance algorithms was implanted. The patients were reassessed 6 months post randomisation. The primary endpoint was LVEF at follow-up calculated as an average over three non-paced, normally conducted beats using modified Simpson’s method as per American Society of Echocardiogrpahy guidelines.^25^ The protocol was tolerated in all but two subjects in whom rate-responsive pacing was reactivated. Nevertheless, application of the protocol reduced absolute RV pacing percentage by a mean of 49% (95% CI 41% to 57%; p<0.0001) from baseline and resulted in a mean absolute improvement in LVEF of 6% (95% CI 2% to 8%; p<0.0001). This occurred without reduction in exercise capacity, NT-proBNP or quality of life. An association was seen between the reduction in RV pacing and magnitude of change in LVEF (p=0.04). The intervention was considered safe to use without adaptation in OPT-PACE.

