## Methods and analysis

OPT-PACE is a multicentre, randomised, non-blinded parallel trial funded by the National Institute for Health Research (NIHR) in the UK (NIHR-CS-2012-032) and registered with the Clinical Trials registry. The trial design and protocol have received approval from necessary regulatory and ethics boards as well as an independent trial steering committee.

The trial will recruit 1200 patients, which began in June 2013 and all patients will be followed up for a minimum of 12 months.

Trial participation may be terminated via voluntary refusal to continue at any time or through significant clinical deterioration assessed by medical staff. Participants suffering from trial-related problems or adverse events (AEs) may obtain medical treatment as compensation, and the trial is insured to compensate.

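### The 15% one-year control rate is not reconciled with the protocol's own pilot data; at the pilot rate, 146 events and 90% power are missed on either reading of follow-up

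*Protocol article*

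**What the plan says.** The Sample size section sets 15% at one year in the standard pathway against 9% in the intervention arm, gives the equivalent HR as 0.58, and specifies a log-rank test at two-sided 5% with "a power of 0.90". It concludes that this "requires a total of 146 events to be observed in at least 1070 participants", assuming recruitment over 18 months, and inflates 1070 to 1200 for drop-out. It does not state the follow-up length used in the calculation.

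The Risk model part of Pilot data describes 491 patients at the tertiary centre, a cohort said to inform the design. For the same composite it reports: "After a mean follow-up time of 668 days, 56 patients (12%) had died or been hospitalised for HF".

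Follow-up is described in three other places:

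- Methods and analysis: "all patients will be followed up for a minimum of 12 months".
- Data collection: "Digital follow-up will occur at 12-month postrecruitment to record mortality and hospitalisation data and changes to medical therapy".
- Statistical analysis plan: Kaplan-Meier estimates, HRs and log-rank tests, with 12-month survival reported.

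**The concern.** The power of a log-rank test depends on the number of events, so it rests on the control event rate and the length of follow-up. The rate assumed is more than twice what the article's own composite data imply, and no reason is given. The follow-up can be read as a fixed 12 months per patient or as a common close at least 12 months after the last entry, and these give very different event counts.

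If the pilot rate is nearer the truth, a real HR of 0.58 would be missed in roughly one trial in five (common close) to more than two in five (12 months only). A null result could then be taken as evidence against screening when the trial was too small to tell.

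**Working it through.** **1. The stated event requirement.** Inputs from Sample size: HR 0.58 (check: ln 0.91 / ln 0.85 = 0.580), two-sided alpha 0.05, power 0.90; 1:1 allocation from Randomisation and interventions.

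- Schoenfeld: 4 × (1.960 + 1.282)² / (ln 0.58)² = 142 events.
- Freedman: (1.58 / 0.42)² × (1.960 + 1.282)² = 149 events.

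The stated 146 lies between them, so it is a sound requirement for that HR.

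**2. Events at the planning rates.** Exponential hazards per year are −ln 0.85 = 0.1625 (control) and −ln 0.91 = 0.0943 (intervention).

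- Fixed 12 months: pooled risk (15% + 9%) / 2 = 12%. Then 1070 × 0.12 = 128 and 1200 × 0.12 = 144 with no drop-out.
- Common close (uniform accrual over 1.5 years, closing 1 year after the last entry): risk per arm = 1 − (e^(−λ) − e^(−2.5λ)) / (1.5λ), which is 24.6% and 15.1%, pooled 19.86%. Then 1070 × 0.1986 = 212 and 1200 × 0.1986 = 238.

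The plan implies 146 / 1070 = 13.6%, which is neither 12% nor 19.9%. Under fixed 12 months, 146 events need 146 / 0.12 = 1217 patients, or about 13.8 months of follow-up in 1070. With 18-month accrual, 146 in 1070 arises only if the last patient is followed about 0.41 years (5 months), below the stated 12-month minimum.

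**3. The pilot rate.** 668 / 365.25 = 1.829 years.

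- Person-time: 56 / (491 × 1.829) = 0.0624 per year; one-year risk 1 − e^(−0.0624) = 6.0%.
- From the printed 12%: −ln(0.88) / 1.829 = 0.0699 per year; one-year risk 6.8%.

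(56 / 491 is 11.4%, not 12%. Using both figures covers the difference.)

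**4. Events and power at the pilot rate.** The intervention hazard is 0.58 × control. Power = Φ(√D / 2 × |ln 0.58| − 1.960), with |ln 0.58| = 0.545.

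Example at 6.0%, fixed 12 months: intervention risk 1 − e^(−0.58 × 0.0624) = 3.55%. D = 1200 × (6.05% + 3.55%) / 2 = 58. Power = Φ(√57.6 / 2 × 0.545 − 1.960) = Φ(0.107) = 54%.

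| Control one-year risk | Follow-up | N | Events | Power |
|---|---|---|---|---|
| 15% | fixed 12 months | 1070 | 128 | 87% |
| 15% | fixed 12 months | 1200 | 144 | 90% |
| 15% | common close | 1070 | 212 | 98% |
| 15% | common close | 1200 | 238 | 99% |
| 6.0–6.8% | fixed 12 months | 1070 | 51–57 | 50–54% |
| 6.0–6.8% | fixed 12 months | 1200 | 58–64 | 54–59% |
| 6.0–6.8% | common close | 1070 | 88–98 | 72–77% |
| 6.0–6.8% | common close | 1200 | 99–110 | 77–81% |

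With no treatment effect at all, the pilot rate in 1200 patients gives 73–81 events (fixed) or 124–138 (common close), still below 146.

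**The case against.** A reader might infer that 146 events cannot be reached, or that the trial falls well short even at its own rates. The documents do not support this. A 12-month minimum, a time-to-event endpoint with no cap and an 18-month recruitment assumption all fit a common close, and at the planning rates that passes 146 comfortably. Only Data collection points to a single capture at 12 months, and it does not say that outcomes are censored there. Even on that reading the planning-rate shortfall is small: 2 events in 1200, or 18 in 1070.

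A reader might also infer that the 15% was taken from the 66-patient reprogramming cohort, because the citation number matches and for that study "The primary endpoint was LVEF at follow-up". But the same citation is attached under Outcome measures to the risk-model pilot analysis, which the Risk model section credits to a different source, so it may be a numbering slip. The cited paper is not shown, so where the 15% comes from cannot be settled.

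Finally, the pilot rate may not carry over. The cohort was single-centre and awaiting generator replacement; its exclusions and the timing of its events are not given. The trial adds two district centres and takes anyone at least 12 months after implant. It also excludes patients already under heart failure services or with life expectancy under a year, but how many of the 491 were such patients is not stated, so no firm direction follows.

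These points limit the claim but do not remove it. The article offers no reason to expect more than twice the rate seen in the cohort it says informed the design.

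**Conclusion.** The point holds in two parts.

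The main one is the control rate. The assumed 15% stands unreconciled against about 6.0–6.8% from the only composite event data in the article. At the pilot rate, both the 146 events and the 90% power are missed on either follow-up reading: a severe loss at fixed 12 months and a moderate one with a common close. This rests on a constant hazard, on the pilot cohort being representative, on HR 0.58 being true, and on all 1200 patients contributing.

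The second part is internal consistency. The pairing of 146 events with 1070 patients fits neither follow-up scheme at the planning rates. That is a fault of specification more than of power, since those rates give about 87–90% power at 12 months and more with a common close. The figure of 146 is itself correct for HR 0.58.

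**What to change.** 1. In Sample size, justify the 15% with an identified source for this composite at one year, or replace it with the rate from the 491-patient cohort. Restate expected events and power over the plausible range.
2. Reconcile Methods and analysis, Data collection, Sample size and Statistical analysis plan by naming one common data cut-off date, with the events and power expected by then.
3. State that all record-based follow-up to that date enters the log-rank and Cox analyses, with 12-month Kaplan-Meier survival as a summary.

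A stop fixed at 146 events is not recommended. That number depends on HR 0.58, whose derivation from the effect in the one third of patients with cardiac dysfunction is a separate question.

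The cost is wording, repeat digital record checks, a less favourable stated power and a later read-out. For scale, 146 events in 1200 patients at the pilot rate and HR 0.58 would take about 2.4–2.6 years of follow-up per patient: at the planning rates it takes 1.015 years, and 1.015 × 0.1625 / 0.0699 = 2.4, or / 0.0624 = 2.6. No extra patients or visits are needed.

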### Statistical analysis plan

Primary analysis will be performed using the prespecified endpoints in the intention-to-treat population (all randomised patients). Time to event will be summarised across randomised groups using Kaplan-Meier estimates, HRs and comparison across groups using log-rank tests, reporting 12-month survival.

Secondary analyses will estimate adjusted treatment effects through Cox proportional hazards regression model to describe the influence of baseline patient characteristics on outcome. Factors to explore include age, gender, site, comorbidities, type of device, New York Heart Association (NYHA) class, medication, blood measures and underlying rhythm. A post hoc exploratory cost-effectiveness analysis will be conducted.

Quality of life data is collected at two time points and will be summarised graphically, conditional on patient survival. Quality-adjusted time to event analysis may be appropriate to report quality-adjusted estimates of 12-month survival.

External validation of the risk model will be based on fitting the published model to the OPT-PACE trial data to report its goodness of fit. Data will be pooled, and stratified by study, to remodel parameter estimates with the aim of improving precision.

### Patient and public involvement

The research question developed as a large number of pacemaker patients was seen in HF clinic with deterioration in their ventricular function and symptoms who were followed-up annually in pacemaker clinic and yet, these had not been detected. The study was initially discussed with a well-established local patient and public involvement (PPI) advisory group (AG) consisting of cardiovascular patients and their families. The AG particularly felt that undergoing all study assessments in 1 day was appealing to potential participants but that the intervention was not a large burden and that it was more important to know the effect on patient survival and the number of times patients were hospitalised, not just whether there was an improvement in heart function from optimised care in terms of outcome measures. Once the final protocol was established, it was reviewed by the PPI-AG along with patient information sheets to ensure the plain English was at an appropriate level. Regular updates will be presented regarding recruitment and any AEs. Study results will be discussed and an appropriate method of dissemination will be designed together between the AG and the researchers to deliver these to participants.

### Ethics and dissemination

Amendments will be documented. Trial results will be communicated on a local level to healthcare professionals and patient involvement groups. Results will be published in international peer-reviewed journals with authorship as determined by the international committee of medical journal editors’ guidelines^30^ and highlighted using social media campaigns. The National Institute of Health Research will be made aware prior to publication but no publication restrictions apply.

